## Intensive PK Specimens

After 4 weeks of dosing on the 100% adherence condition, all participants will undergo a 24 hour intensive-PK study protocol (requiring an approximately 25-hour-long hospital stay) to evaluate steady-state effects of TFV in plasma. This visit will take place at the Clinical Resource Center (CRC) associated with UCSF/Moffitt Hospital.

The participant’s usual diet will be ascertained by phone prior to the PK visit, and simulation of the usual diet will be undertaken in the CRC during PK sampling. During the week before the PK study visit, the participant will complete questionnaires ascertaining current medication and substance use patterns, current dietary patterns, and current menstrual, contraceptive, and obstetric history, if applicable. An initial blood level will be drawn (“0” timepoint) and consumption of one dose of oral tenofovir will be witnessed. A series of blood samples will then be collected into EDTA tubes at 0, 0.25, 0.5, 1, 1.5, 2, 3, 4, 6, 8, 10, 12, 16, and 24 hours post-dose after witnessed dosing.

## PBMC Specimens

Peripheral blood mononuclear cells (PBMCs) will be collected at enrollment and at the 6 week visits for each dosing condition. PBMCs will be used to determine association between dose and intracellular tenofovir diphosphate (TFV-DP) levels, correlating TFV hair levels with TFV-DP levels, performing pharmacogenomic studies on the influence of single-nucleotide polymorphisms on TFV levels, and conducting in vitro challenge experiments to determine minimum inhibitory TFV dose required to inhibit viral replication (section 8.9).

## HIV-1 Cultures of PBMCs in vitro

Surrogate markers of the protective effects of tenofovir are needed to facilitate future optimization of chemoprophylaxis dose.  We hypothesize that drug dose, hair drug levels, or intracellular drug levels in this study will correlate with susceptibility of blood cells to HIV-1 measured ex vivo.  Peripheral blood mononuclear cells will be processed at the UCSF Laboratory of Clinical Virology using methods that yield specimens that are suitable for viral culture (i.e.: separation over ficoll hypaque).  These cells will be stimulated in vitro possibly using PHA or anti-CD3 antibodies in IL-2 containing media.  If required to allow viral replication, CD8 cells will be depleted from the cell specimens using anti-CD8 antibodies.  The stimulated cells will be challenged with a dilution series of a standardized stock of HIV-1 to determine the infectious dose sufficient to infect 50% of the culture wells (TCID50).  Viral challenges will occur within 24 hours of cell culture to minimize the decay of drug concentrations inside the cells.  Standard approaches to evaluate viral replication will be used, and may include measurement of p24 antigen in the culture supernatant or detection of markers expressed by viral test vectors, such as luciferase or GFP.  All work will be performed under a current UCSF approved BUA in the laboratory.  Participants will not be exposed to HIV-1 during these procedures; rather, the blood cells obtained by phlebotomy will be analyzed ex vivo in the laboratory.  No participant identifiers will be shared with the laboratory.  The viral culture assays are not validated for clinical use so individual results will not be shared with the study participants.  Values obtained using cells derived during therapy will be compared with values obtained using cells prior to therapy to estimate the fold change in TCID50 associated with every dosage level and intracellular TNF-DP level.

## Additional Cryopreservation of Blood Specimens

At visits where PBMCs are collected, leftover plasma specimens will be cryopreserved for future testing. These specimens may be used for (1) analysis of plasma TDF levels, (2) analysis of lipids and other parameters of lipid or glucose metabolism, (3) testing for additional markers of renal function, such as cystatin C, and (4) testing of markers of bone turnover. In addition, serum will be storage at visits where blood is drawn for possible future testing of novel markers of renal function (Cystatin C) and markers of bone turnover.

# ADVERSE EVENTS

An adverse event (AE) is any untoward medical occurrence in a clinical research participant enrolled in a clinical trial, regardless of causality assessment. An AE can be any unfavorable or unintended sign, symptom, or disease temporally associated with the use of an investigational product or study participation, whether or not considered related to the product or study participation. Pre-existing conditions, which increase in frequency or severity or change in nature during or as a consequence of use of a drug in human clinical trials, will also be considered as adverse events. AEs may also include pre- or post-treatment complications that occur as a result of protocol-mandated procedures. AE assessment will begin at the time of randomization, and conditions noted prior to randomization will be noted as pre-existing conditions.

## Assessment of Adverse Events

Study participants will be provided instructions for contacting the study site to report any untoward medical occurrences they may experience, except for possible life-threatening events, for which they will be instructed to seek immediate emergency care. With appropriate permission of the participant, and whenever possible, records from all non-study medical providers related to untoward medical occurrences will be requested and required data elements will be recorded on study CRFs and/or in the participant’s medical chart. All AEs will be followed clinically, until the AE resolves or stabilizes as per the appropriate toxicity algorithm.

## Serious Adverse Event

Serious adverse events (SAEs) will be defined per CFR 312.32 guidelines, as AEs occurring at any dose that:

- Result in death
- Are life-threatening adverse events
- Require inpatient hospitalization or prolongation of existing hospitalization
- Result in persistent or significant disability/incapacity, or
- Are congenital anomalies/birth defects

Important medical events that may not result in death, be life-threatening, or require hospitalization may be considered serious when, based upon appropriate medical judgment, they may jeopardize the participant or require medical or surgical intervention to prevent one of the outcomes listed above.

## Serious Adverse Event Reporting Requirements

All serious adverse events will be reported to the principal investigator within 72 hours of knowledge of the SAE. In addition, all grade 3 or higher adverse events and all creatinine elevations ≥ 0.5 mg/dL over baseline will be reported to the medical officer within this timeframe (72 hours of knowledge). These events may be reported via telephone or email. For hospitalizations, fatal, or life-threatening events, copies of hospital reports, autopsy reports, and other documents will be requested. The investigator will identify all therapeutic measures necessary for resolution of these events. Follow-up of these events will continue until the medical officer determines that the condition has stabilized or resolved.

This study will follow UCSF CHR reporting requirements for adverse events. All serious or unexpected adverse events that are definitely, probably, or possibly related to study participation will be reported to the UCSF IRB within 10 working days of site awareness. The NIMH Project Officer will be provided copies of these reports and informed of any actions taken by the IRB as a result of such events. Finally, Gilead will be notified of all SAEs that may be related to study drug (probably not related, possibly related, probably related, and definitely related).

## Recording of Clinical and Laboratory AEs

All clinical AEs will be assessed by a licensed clinician and recorded on the study Illness/AE log CRF. Laboratory values will be captured and graded in a laboratory database. The following laboratory abnormalities will be recorded on the AE CRFs: 1) grade 2 or higher laboratory AEs on the DAIDS toxicity table, 2) laboratory AEs that result in study drug interruption or discontinuation, require a concomitant medication, or are associated with symptoms, or 3) laboratory AEs that the investigator or clinician feels are clinically significant. If the laboratory abnormality is part of a syndrome, the overall syndrome or diagnosis will be recorded.

## Adverse Event Relationship to Study Product

The relationship of all AEs to study product will be assessed per the Manual for Expedited Reporting of Adverse Events to DAIDS (dated 6 May 2004), the package insert and investigator’s brochure for Viread, and clinical judgment of the investigator. The relationship categories that will be used for this study are:

- Definitely related: adverse event and administration of study agent are related in time, and a direct association can be demonstrated with the study agent
- Probably related: adverse event and administration of study agent are reasonably related in time, and the adverse event is more likely explained by the study agent than by other causes
- Possibly related: adverse event and administration of study agent are reasonably related in time, and the adverse event can be explained equally well by causes other than the study agent.
- Probably not related: a potential relationship between administration of study product and adverse event could exist, but is unlikely, and the adverse event is most likely explained by causes other than the study agent
- Not related: the adverse event is clearly explained by another cause unrelated to administration of the study product. Reportable events must have documentation to support the determination of “not related.”

## Grading Severity of Adverse Events

All AEs and abnormal laboratory values will be graded using the NIAID DAIDS AE Grading Table (Appendix 2). For laboratory AEs where there is a gap between grades (i.e. for creatinine grade 1 AE = 1.43 – 1.69 mg/dL, and grade 2 range = 1.82 – 2.34 mg/dL for ULN = 1.3), the higher grade will start at the upper limit of the lower grade (grade 2 creatinine elevation will be begin at 1.70 mg/dL).

## Toxicity Management

In general, the site investigator has the discretion to hold study product at any time if he feels that continued product use would be harmful to the participant or interfere with treatment deemed clinically necessary according to the judgment of the investigator. Clinical or laboratory abnormalities that require follow up will be documented, and the research associate or clinician will contact the participant to schedule an interim visit for follow-up and/or repeat laboratory testing. All participants reporting an untoward medical occurrence will be followed clinically until the occurrence resolves (returns to baseline grade, defined as grade at enrollment) or stabilizes.

Grade 1 and 2 Laboratory Abnormality or Clinical Event (excluding creatinine elevations)

Continue study product at the discretion of the site investigator.

Grade 3 Laboratory Abnormality or Clinical Event (excluding creatinine elevations)

Study medication may be continued at the discretion of the site investigator if a grade 3 toxicity is considered to be unrelated or probably not related to the study medication. Study medication will be temporarily withheld if Grade 3 toxicity is considered to be possibly related, probably related, or definitely related to the study medication. Laboratory toxicity will be promptly confirmed by repeating the test on an additional specimen, preferably within 7 days. After a Grade 3 toxicity returns to Grade 1, the participant can be reintroduced to medication. If a Grade 3 toxicity recurs and is considered to be probably or definitely related to study medication, the study medication will be permanently discontinued.

Grade 4 Laboratory Abnormality or Clinical Event (excluding creatinine elevations)

For all Grade 4 laboratory-identified or clinical toxicities, the study medication will be withheld. Laboratory toxicity will be promptly confirmed by repeating the test on an additional specimen, preferably within 7 days. If a grade 4 laboratory toxicity is not confirmed by repeat testing, it should be managed per algorithm for the new toxicity grade. Participants with grade 4 AEs will be followed until the event resolves to baseline or stabilizes. If a grade 4 toxicity is considered to be unrelated or probably not related to study product and resolves to baseline, study drug may be restarted at the discretion of the site investigator. If the toxicity recurs to grade 3 or higher after study medication is restarted and is considered to be probably or definitely related to study medication, the study medication will be permanently discontinued.

### Creatinine Elevations

For creatinine elevations ≥ 0.5 mg/dL over baseline creatinine (at enrollment), serum creatinine will be repeated as soon as possible, preferably within 7 days, and the protocol chair or designated medical officer will be notified within 72 hours. Study product will be held for confirmed creatinine elevations ≥ 0.5 mg/dL over baseline or creatinine clearance < 50 mL/min. Study product should be held until creatinine returns to within 0.3 mg/dL of enrollment level, at which point the participant may be rechallenged with study drug after consultation with the protocol chair. If serum creatinine rises again to ≥ 0.5 mg/dL over baseline or creatinine clearance drops to below 50 mL/min when drug is restarted, study product should be permanently discontinued, and the participant will be monitored until level returns to baseline (enrollment value) or stabilizes.

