## Inclusion Criteria

Men and women must meet all of the following criteria to be eligible for inclusion in the study:

- Age 18 or older
- Willing and able to provide written informed consent
- Ability to speak English
- HIV-1 uninfected based on HIV rapid testing performed during screening and enrollment
- Calculated creatinine clearance ≥ 60 mL/min by the Cockcroft-Gault Creatinine Clearance Formula where creatinine clearance in mL/min is calculated as follows:

Male: [(140 - age in years) x (wt in kg)] / [72 x (serum creatinine in mg/dL)]
Female: [(140 - age in years) x (wt in kg) x 0.85] / [72 x (serum creatinine in mg/dL)]

- Serum creatinine less than or equal to the site laboratory upper limit of normal (ULN)
- Urine dipstick with negative or trace result for both glucose and protein
- Negative urine ß-HCG test (for women)
- Adequate hepatic function (total bilirubin and hepatic transaminases (ALT and AST) ≤ 2x ULN)
- Adequate hematologic function (absolute neutrophil count ≥ 1,500/mm^3^, platelets count ≥ 100,000/mm^3^, and hemoglobin ≥ 10 g/dL)
- Ability to participate in modified directly observed dosing of study drug
- Able to provide a personal cell phone number to be contacted on for unobserved mDOT visits
- Minimum length of 3 cm scalp hair in occipital region
- Willing to provide hair and plasma samples per protocol
- Dark hair (brown or black) assessed by the study clinician.
- Reproductive status: A volunteer who was born female must:
  - Agree to consistently use effective contraception from at least 21 days prior to enrollment through the last protocol visit for sexual activity that could lead to pregnancy. Effective contraception is defined as using any of the following methods:
    - Condoms (male or female) with or without a spermicide
    - Diaphragm or cervical cap with spermicide
    - Intrauterine device (IUD)
    - Hormonal contraception, or
    - Successful vasectomy in the male partner (considered successful if a volunteer reports that a male partner has [1] documentation of azoospermia by microscopy, or [2] a vasectomy more than 2 years ago with no resultant pregnancy despite sexual activity post-vasectomy);
  - Or not be of reproductive potential, such as having reached menopause (no menses for 1 year) or having undergone hysterectomy, bilateral oophorectomy, or tubal ligation
  - Or be sexually abstinent.

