## Follow-up Visits

Follow-up procedures at each visit are shown in Section 7.1. Adverse event assessments and symptom-directed physical exams will be performed by the study clinician every 3 weeks and additionally as needed during the study. The window period for scheduled study visits will be ± 5 days of the target visit date. Dosing will be continued at the assigned dosing frequency up until the endpoint visit occurs. No further doses for that dosing period will be given after the endpoint visit. HIV rapid testing and safety laboratory monitoring will also occur during these visits, and abnormal lab values will be followed clinically until stabilized. Adherence counseling will be performed at these visits. A hair sample will be collected on the last day of each treatment condition. Plasma samples for the intensive PK study will be collected after 4 weeks of dosing on the 7 doses/week condition.

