## Follow-up Procedures for Participants who Discontinue Study Product

Participants who discontinue study product will be encouraged to remain in the study if they are willing, for safety evaluations every 3 weeks according to the follow-up schedule in section 7.1. Since these participants will be off study drug, they will not complete directly observed or phone mDOT dosing visits. All study procedures described in the early study termination visit (in section 7.12) will be performed at the study drug discontinuation visit, including **hair** collection and PBMC**,** plasma, and serum collection. In addition, if a participant is advised to discontinue study drug by a clinician or the Principal Investigator during a dosing cycle due to an intercurrent illness, adverse event, or other circumstance, the participant may restart the unfinished dosing cycle at a later date if determined to be safe and appropriate by the Principal Investigator and allowable per protocol. Upon restarting the interrupted dosing cycle the participant would be required to complete the cycle in its entirety. This would include a start visit, midpoint visit, and an endpoint visit including all procedures and safety lab tests that are performed at each of these clinical visits. The process of repeating a dosing cycle will be at the discretion of the Principal Investigator. Participants who discontinue study drug and do not restart the dosing cycle will not participate in the intensive PK assessment after study drug discontinuation.

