## Management of Intercurrent Medications

Participants who begin taking any medication during the trial that is listed as an exclusionary medication at screening will temporarily discontinue study drug. Study drug may be resumed if no exclusionary medication has been taken in the last 4 weeks, serum creatinine is within 0.3 mg/dL of enrollment level, and a rapid test for HIV antibodies is negative.

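### Section 9.7.1 holds study product for creatinine clearance below 50 mL/min but states release in creatinine alone, so near the 60 mL/min entry limit both conditions can be met at once

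*Protocol*

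**What the plan says.** Entry requires "Calculated creatinine clearance ≥ 60 mL/min" by Cockcroft-Gault and serum creatinine no higher than the site laboratory's upper limit of normal (Protocol 5.3).

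Protocol 9.7.1 then sets three steps:

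- **Hold.** "Study product will be held for confirmed creatinine elevations ≥ 0.5 mg/dL over baseline or creatinine clearance < 50 mL/min".
- **Release.** Product is "held until creatinine returns to within 0.3 mg/dL of enrollment level, at which point the participant may be rechallenged with study drug after consultation"; the person consulted is the protocol chair.
- **Permanent stop.** After restart, a renewed rise of at least 0.5 mg/dL is one ground. Clearance is the other: if "creatinine clearance drops to below 50 mL/min when drug is restarted, study product should be permanently discontinued".

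Clearance therefore appears in the first and third steps but not in the second. No other section supplies a clearance value for restart. Section 7.11 allows an interrupted cycle to be repeated "if determined to be safe and appropriate by the Principal Investigator and allowable per protocol", which leads back to 9.7.1. Section 9.8, on resuming after an excluded medication, also states its renal condition in creatinine: "serum creatinine is within 0.3 mg/dL of enrollment level, and a rapid test for HIV antibodies is negative".

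**The concern.** A release condition should undo the trigger that caused the hold. Creatinine within 0.3 mg/dL of enrollment does this for the 0.5 mg/dL trigger. It need not do so for the clearance trigger. In someone who enters with little reserve above 60 mL/min, a creatinine rise that stays inside the 0.3 mg/dL band can take clearance below 50. The release condition is then already satisfied when the hold begins.

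The stake is participant safety. Section 11.4 lists renal impairment among the rare but serious risks of the drug, and section 11.5 expects no direct benefit for volunteers. If rechallenge went ahead below 50 mL/min, the participant would already be at the level that the permanent-stop sentence names. The text does not say whether such a person meets that ground at once or has not dropped below a limit that was never regained.

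**Working it through.** The protocol gives no figure of its own on this point, so there is nothing to reproduce. The check applies its formula to its thresholds.

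**Inputs from the protocol**

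- Clearance = (140 - age) x weight / (72 x creatinine), multiplied by 0.85 for women (5.3).
- Entry limit 60 mL/min (5.3); hold limit 50 mL/min and release limit a rise of 0.3 mg/dL (9.7.1).

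**Assumptions**

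- Baseline creatinine S0 of 0.8, 1.0 or 1.3 mg/dL. The protocol gives no baseline values. The 1.3 is the upper limit of normal used as a grading example in 9.6, not a stated site limit.
- Age and weight unchanged between enrollment and the hold.

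**Formulas.** With age, weight and sex fixed, clearance is proportional to 1/creatinine. With C0 the entry clearance, after a rise d it is C0 x S0/(S0 + d).

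- Hold by clearance: d > S0 x (C0/50 - 1).
- Release: d ≤ 0.3.
- Both are possible when S0 x (C0/50 - 1) < 0.3, that is, C0 < 50 x (1 + 0.3/S0).

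**Results**

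| | S0 = 0.8 | S0 = 1.0 | S0 = 1.3 |
|---|---|---|---|
| Rise that brings clearance from 60 to 50: 0.2 x S0 (mg/dL) | 0.16 | 0.20 | 0.26 |
| Clearance at a rise of 0.3 from entry at 60: 60 x S0/(S0 + 0.3) (mL/min) | 43.6 | 46.2 | 48.8 |
| Entry clearance below which both can hold: 50 x (1 + 0.3/S0) (mL/min) | 68.8 | 65.0 | 61.5 |

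Lower baselines widen the window. For entry at exactly 60 mL/min it closes only at S0 = 1.5 mg/dL, where 0.2 x 1.5 = 0.30.

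**An example with overlap.** A woman aged 55, 55 kg, creatinine 0.90:

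- At entry: 85 x 55 x 0.85 / (72 x 0.90) = 61.3 mL/min. She meets the clearance criterion.
- At creatinine 1.15 (rise 0.25): 85 x 55 x 0.85 / (72 x 1.15) = 48.0 mL/min. She is below the hold limit and inside the release band.

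**An example without overlap.** A man aged 60, 70 kg, creatinine 1.2:

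- At entry: 80 x 70 / (72 x 1.2) = 64.8 mL/min.
- At a rise of 0.3: 80 x 70 / (72 x 1.5) = 51.9 mL/min, still above the hold limit.

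The overlap is therefore real, but confined to people who enter just above the limit.

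**The case against.** The strongest reply is that the hold trigger keeps applying. Nothing in 9.7.1 says that the release sentence overrides it. The release sentence sets a minimum and then only permits rechallenge, after consultation with the protocol chair. Its wording also presupposes that creatinine left the 0.3 mg/dL band before coming back. The permanent-stop sentence shows that dosing below 50 mL/min is not intended.

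There are further safeguards. The investigator may hold product at any time, and staff "will contact the participant to schedule an interim visit for follow-up and/or repeat laboratory testing" where an abnormality needs follow-up (9.7). At scheduled visits "abnormal lab values will be followed clinically until stabilized" (7.7). Chemistries are taken at the first-dose visit (7.1), repeating a cycle needs the principal investigator's judgment (7.11), and adverse events are reviewed weekly (9.12).

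Much of this stands. A reader might infer that the release and permanent-stop sentences contradict each other, or that the protocol directs dosing below 50 mL/min. The text supports neither: a permission can be read beside a continuing hold, so both sentences can be followed. A reader might also infer that 9.8, or the 7-day repeat and 72-hour notice for creatinine rises, are defective too. But 9.8 covers a different situation and does not suspend the clearance hold, and the timing targets are not part of this gap.

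What the objection does not do is supply a recovery value. If the release condition counts as met, rechallenge may be considered below the hold limit. If it does not apply to someone whose creatinine never left the band, a clearance-only hold has no written release criterion. Either way, recovery of clearance is left to individual judgment.

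**Conclusion.** The concern holds as a gap in a stated safety rule, with low severity. The release condition does not fit a hold triggered by clearance alone. Read literally, it permits rechallenge to be considered while clearance is below the hold limit and at the level treated as a ground for permanent discontinuation.

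The window runs from 60 up to 68.8, 65.0 or 61.5 mL/min at entry for baselines of 0.8, 1.0 or 1.3 mg/dL. At entry of 60, clearance at the release limit is about 1 to 6 mL/min under the hold limit. These sizes depend on the assumed baselines. The protocol gives no distribution of clearance, so the number of people affected cannot be stated; among 24 healthy volunteers it is likely to be few, if any. The primary hair-concentration endpoint is not affected.

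**What to change.** In 9.7.1 only, make release conditional on both creatinine within 0.3 mg/dL of enrollment and calculated clearance of at least 50 mL/min. Keep the consultation with the protocol chair.

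With a 50 mL/min condition the overlap disappears. For entry at 60 mL/min the residual rise allowed at release becomes the smaller of 0.3 and 0.2 x S0: 0.16, 0.20 or 0.26 mg/dL at baselines of 0.8, 1.0 or 1.3.

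Release at exactly 50 leaves no margin above the permanent-stop limit, so the sponsor's clinicians may prefer a higher value, such as the 60 mL/min entry limit. The price is that someone who entered at exactly 60 would have to return fully to the enrollment creatinine, since S0 x (60/60 - 1) = 0.

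The cost is one phrase in a minor amendment, which needs ethics committee approval before use (11.1), and a slightly longer hold for a few participants. No new test is needed, because clearance is calculated from creatinine already measured.
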